### Data analyses

Analysis will be based on randomization of classrooms to TeachTown (*n* = 35) or control (*n* = 34). Outcomes will be analyzed at the student level across time. Outcome differences will be estimated with longitudinal nested linear models with random effects for classroom and student [49–51]. All outcome measures are continuous variables.

We also will examine several potential moderators of TeachTown impact, including: (1) symptoms at baseline (measured by the PDDBI); (2) cognitive functioning at baseline (measured by the DAS); (3) penetration (whether the consented student received TeachTown instruction based on the electronic logs); (4) fidelity of program implementation (direct observation of generalization lessons, described in aim 2); (5) use of the EBPs described in Aims 3; and (6) family characteristics, including family composition and parent education and income. Potential moderators will be included in the model as main effects and as interaction terms with time and treatment group factors in the model. The three-way interaction between time, treatment group, and the moderator will be used to assess the presence and magnitude of the moderating effect. Because both TeachTown and EBP fidelity may vary over the course of the year for each student, we will use growth mixture models to categorize fidelity trajectories at the student level.

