### Measures

Our primary outcome of interest, in keeping with recent randomized trials of autism interventions, is cognitive gain. Other selected measures are tied to the domains in which TeachTown purports to affect change (see Table 1).

**Table 1 Tab1:** List of measures, respondents, and time points for data collection

Measure	Respondent	Time point
Aim 1: Effectiveness		
Differential Ability Scales, 2nd Edition (DAS-II)	Direct observation of student functioning completed by graduate student or clinician	Beginning and end of year 1
Bracken Basic Concept Scales, 3rd Edition	Direct observation of student functioning completed by graduate student or clinician	Beginning and end of year 1
Autism Diagnostic Observation Schedule—2nd edition (ADOS-2)	Direct observation of student functioning completed by graduate student or clinician	Throughout year 1
Adaptive Behavior Assessment System, 2nd Edition (ABAS-II)	Teacher rating form of child functioning	Beginning and end of year 1
Pervasive Developmental Disorder Behavior Inventory (PDD-BI)	Teacher rating form of child functioning	Beginning and end of year 1
Social Communication Questionnaire (SCQ)	Parent rating form of child functioning	Beginning of year 1
Family Demographic Questionnaire	Parent	Beginning of year 1
Teacher Demographic Questionnaire	Teacher	Beginning of year 1
Aim 2: Implementation		
TeachTown penetration	Computer software logs	Monthly
TeachTown fidelity	Direct observation of teacher behavior conducted by TeachTown staff	Monthly
Intentions and attitudes scale	Teacher rating scale	Mid-year years 1 and 2
Aim 3: Exnovation		
Existing EBP fidelity	Direct observation of teacher behavior conducted by trained research assistants	Monthly

*Cognitive ability* will be assessed using the Differential Ability Scales, 2nd Edition (DAS-II) [41]. The DAS-II assesses cognitive abilities that are important to learning and may be administered to children ages 2 years 6 months through 17 years 11 months across a broad range of developmental levels. A member of the assessment team will administer the DAS-II to students in the study at the beginning and end of the academic year in year 1.

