#### *Statistical power for quantitative analyses*

The prior trial of TeachTown reports that students made gains in communication skills of a moderate effect [71]. Meta-analytic reviews of studies of other interventions for children with ASD report large intervention effects [4, 72–74]. Based on this literature, we conducted a power analysis to determine the effect sizes we could expect in our cluster randomized study of students nested within the 70 classrooms in the district. Using the Power and Precision software package [75], we calculate that for student outcomes we will have power of 80% to detect a moderate intervention effect of *d* = 0.43, assuming enrollment of four students per classroom, an intraclass correlation (ICC) of 0.2, and inclusion of one covariate in our regression model that explains 15% of the variation. For teacher outcomes, we will have 80% power to detect a larger effect of the intervention (*d* = .7) assuming a model with a single covariate (*r*
^2^ = .15). All models assume two tailed tests with alpha = 0.05.

Our secondary goal is to test the potential impact of moderating factors. With the proposed sample size, the study will have power of 80% to identify an effect size associated with moderators of *d* = 0.65 [71], a moderate-to-large effect. For teacher-level analyses, we are powered to test moderators with an effect size of *d* = 0.85, a large effect.

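### The primary analysis (a longitudinal model with no covariate named) and the power calculation (a regression with one covariate) describe different models; read as a plain time-by-arm contrast, the analysis gives up precision that the baseline DAS-II already offers

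*Protocol article*

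**What the plan says.** The Measures section under Aim 1 states: "Our primary outcome of interest, in keeping with recent randomized trials of autism interventions, is cognitive gain". The DAS-II is given at the beginning and end of year 1, so there are two time points.

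The Data analyses section under Aim 1 (35 TeachTown and 34 control classrooms) says that outcomes are analysed per student over time, and: "Outcome differences will be estimated with longitudinal nested linear models with random effects for classroom and student". It does not write out the main contrast. It adds moderators to a model that already holds time and treatment-group factors, and tests them by a time × group × moderator interaction. Baseline DAS-II appears in that section only as a moderator.

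The power section claims "power of 80% to detect a moderate intervention effect of *d* = 0.43" for "students nested within the 70 classrooms in the district", "assuming enrollment of four students per classroom", with "an intraclass correlation (ICC) of 0.2" and "inclusion of one covariate in our regression model that explains 15% of the variation". It adds: "All models assume two tailed tests with alpha = 0.05". It does not name the covariate, gives no pre-post correlation, and does not say whether the ICC belongs to the end-of-year score or to the gain.

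**The concern.** A regression with one covariate and a longitudinal model with time and group are different analyses and need different inputs. The power of a gain contrast over two time points depends on the pre-post correlation and on how strongly gains cluster by classroom. Neither is given, so the printed power cannot be tied to the planned model.

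The wording also points to a model in which the arms may have different baseline means, since treatment group is itself a factor. With two time points, the time-by-arm term of such a model is the difference in mean gain. Randomisation gives the arms the same expected baseline, and the baseline DAS-II is collected anyway. A gain contrast does not make full use of either fact. At stake is precision on the primary outcome, which costs nothing to recover.

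**Working it through.** **Inputs from the protocol.** d = 0.43; m = 4 students per classroom; ICC = 0.2; covariate R² = 0.15; two-sided alpha 0.05; 70 classrooms (power section, taken as 35/35) or 35/34 (Data analyses).

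**Assumptions, not in the protocol.** Equal SDs at both time points; d in end-of-year SD units; ICC 0.2 also for gains; r varied from 0.3 to 0.8.

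**Formula.** SE² = [ICC + (1 − ICC)/m] × (1/J1 + 1/J2) × V, with power from the noncentral t (classrooms minus 2 df, or minus 3 with a covariate). The bracket is 0.2 + 0.8/4 = 0.4. V is 1 for end-of-year scores alone, 0.85 with a covariate explaining 15% at both levels, 2(1 − r) for the gain, and 1 − r² with baseline adjustment.

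**Step 1: the printed figure.**
- No covariate, 35/35: SE = √(0.4 × 2/35) = 0.151; 0.43/0.151 = 2.84; power 80.1%. With 35/34 it is 79.5%.
- 15% covariate at both levels, 35/35: SE = 0.151 × √0.85 = 0.139; 0.43/0.139 = 3.08; power 86.0% (detectable d = 0.396). With 35/34 it is 85.5%.
- 15% at one level only, 35/35: power 83% (detectable d = 0.413).

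So the pair d = 0.43 and 80% is the no-covariate result, and does not match the power section's own description.

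**Step 2: precision, gain against baseline adjustment.** The ratio of variances is (1 − r²)/[2(1 − r)] = (1 + r)/2, so adjustment removes a fraction (1 − r)/2. With unequal SDs, the gain variance exceeds the adjusted variance by (SD_pre − r × SD_post)², which is never negative. Apart from one degree of freedom, the gain contrast is therefore never the more precise of the two.

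**Step 3: power with 35/34 classrooms.**

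| r | V gain | V adjusted | variance cut | power, gain | power, adjusted |
|---|---|---|---|---|---|
| 0.3 | 1.40 | 0.91 | 35% | 65% | 83% |
| 0.387 (√0.15) | 1.225 | 0.85 | 31% | 71% | 85% |
| 0.5 | 1.00 | 0.75 | 25% | 79% | 89% |
| 0.6 | 0.80 | 0.64 | 20% | 88% | 94% |
| 0.7 | 0.60 | 0.51 | 15% | 95% | 97% |
| 0.8 | 0.40 | 0.36 | 10% | 99% | above 99% |

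**Step 4: sensitivity to the ICC of the gain.** At r = 0.387 with 35/34, the gain contrast has 71% power at gain ICC 0.2, 79.6% at 0.10 and 84% at 0.05.

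**Step 5: random intercepts only.** If the classroom and student effects are intercepts and nothing more, the classroom effect cancels from the time-by-arm contrast. At r = 0.387, nominal power is then about 90%, but the standard error ignores any variation between classrooms in gain. If gains do have ICC 0.2, the omitted design effect is 1 + 3 × 0.2 = 1.6, and a nominal 5% test has a true size of about 12% (1.96/√1.6 = 1.55).

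**The case against.** The strongest reply is that a journal article condenses the full plan. It describes the model in one sentence, does not exclude covariates, and never writes out the main contrast. A longitudinal model with equal baseline means fits the sentence and is about as precise as baseline adjustment. A gain contrast is also unbiased under randomisation and agrees with the declared outcome.

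Much of this stands. The unconstrained contrast is inferred, although gain as the outcome, treatment group as a model factor and the three-way interaction all point to it. The precision loss also shrinks as r rises. What remains is that the article itself states two models that differ, and that the printed power does not match the covariate it describes. Neither is a matter of omitted detail.

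A reader might go further and infer that the planned analysis has only about 71% power on the plan's own 15% figure. The protocol does not support that. The 71% needs the unnamed covariate to be the baseline score (r = √0.15 = 0.387), a gain ICC of 0.2, and d in end-of-year SD units. It rises to about 80% at r = 0.5 or at gain ICC 0.10. If d = 0.43 is instead in gain-SD units with ICC 0.2, the gain contrast has the printed power (80.1% with 35/35, 79.5% with 35/34). Nor does dropping the covariate cost anything against the printed figure, because that figure already corresponds to no covariate.

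**Conclusion.** The point holds as a mismatch and an avoidable loss of precision, not as a demonstrated power deficit. The Data analyses and power sections do not describe the same model, and the power section's 80% at d = 0.43 does not follow from its stated covariate (about 86% if it acts at both levels, 83% if at one).

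If the analysis is an unconstrained time-by-arm contrast, baseline adjustment cuts the variance by (1 − r)/2: 31% at r = 0.39, falling to 10% at r = 0.8. That result needs equal SDs and the same ICC for both analyses; it does not depend on what the 15% covariate is. Power of the gain contrast can be given only as a range, from 65% at r = 0.3 to 95% at r = 0.7 under the assumptions listed. A shortfall against 80% would need r below about 0.5 together with a gain ICC near 0.2 and d in end-of-year units. The change is worth making because it is free.

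**What to change.** In the Data analyses section under Aim 1, define the primary estimate as the arm difference in end-of-year DAS-II adjusted for the student's baseline DAS-II, from a linear mixed model with a classroom random effect. Alternatively, keep the longitudinal model with the two arms' baseline means constrained equal, and add a classroom-by-time random effect so that clustering of gains enters the standard error. Do the same for the Bracken, ABAS-II and PDD-BI.

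In the power section, name the baseline score as the covariate, state the assumed pre-post correlation and the quantity to which the ICC applies, and restate the power or detectable d for that model, using one classroom count throughout (70 or 69).

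The cost is wording and one recalculation, with no new data. The constrained longitudinal form also keeps students who have only one assessment.

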#### Children and their families

By district regulation, children in K-2 autism support classrooms will be between the ages of 5 and 8. The recruitment goal for the study is 4–5 students in each of the 69 classrooms (which usually have 8 students), for a total of 276 participants. Inclusion criteria are that children have an educational classification of autism and be enrolled at least half time in a K-2 autism support classroom. The one exclusion criterion is if the primary caregiver does not speak English or Spanish, which would exclude <1% of eligible participants.

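### As worded, the primary model has no classroom-by-time random effect; fitted with random intercepts only, it would test the effect on cognitive gain without allowing for classroom clustering of gains

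*Protocol article*

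**What the plan says.** In the protocol article, Aim 1, Data analyses, the analysis rests on "randomization of classrooms to TeachTown (*n* = 35) or control (*n* = 34"). The same section adds: "Outcomes will be analyzed at the student level across time". The model is described as "longitudinal nested linear models with random effects for classroom and student". It does not say whether these effects are intercepts only, and it mentions no classroom-by-time term.

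The Measures section states: "Our primary outcome of interest, in keeping with recent randomized trials of autism interventions, is cognitive gain". For that outcome, assessors are to "administer the DAS-II to students in the study at the beginning and end of the academic year in year 1", so there are two time points.

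The primary contrast is not named. The moderator paragraph points to it: "The three-way interaction between time, treatment group, and the moderator will be used to assess the presence and magnitude of the moderating effect". Without the moderator, the matching treatment effect is arm × time.

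The power section is computed "assuming enrollment of four students per classroom, an intraclass correlation (ICC) of 0.2", so it does allow for classroom clustering. The section on children and families gives the sample as "for a total of 276 participants", which is 69 classrooms of 4.

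**The concern.** With two measurements per student, a classroom intercept and a student intercept each add the same amount to both scores and vanish from the difference. Any variation between classrooms in gain falls into the residual. There it is treated as independent from student to student, when classmates in fact share it. The unit of randomization then plays no part in the standard error of arm × time.

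The article itself gives reasons to expect some clustering of gains. Teachers deliver the offline lessons, use and fidelity are expected to differ between teachers, and fidelity and use of existing practices are listed as moderators of impact. For the ABAS-II and PDD-BI, the classroom teacher also rates every enrolled student at both waves.

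At stake is the 5% two-sided level of the primary DAS-II comparison, and of the Bracken, ABAS-II and PDD-BI comparisons if they use the same model. Planning and testing would also be out of step: the sample size pays for clustering and the test would not.

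**Working it through.** **Inputs from the article.** 35 v 34 classrooms (Data analyses); 276 students, so m = 4 (Children and their families; power section); 70 classrooms, ICC 0.2, detectable d = 0.43, 80% power, two-sided alpha 0.05 (power section). **Assumed:** the ICC of gains within classroom, ρ, which the article does not give; range 0 to 0.30.

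**Step 1: reproduce the plan's figure.** In SD units, SE = √(4/J × [ICC + (1 − ICC)/m]) = √(4/70 × [0.2 + 0.8/4]) = √(0.05714 × 0.4) = 0.151. The normal approximation gives a detectable d of (1.960 + 0.842) × 0.151 = 0.424. A noncentral t with 68 df gives 0.430, with power 80.1% at d = 0.43. The stated figure is reproduced with a design effect of 1 + 3 × 0.2 = 1.6 and no credit for the covariate. Crediting R² = 0.15 to the total variance would lower d to 0.39–0.40, so the stated figure is, if anything, conservative.

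**Step 2: what the intercept-only model tests.** For student i in classroom j, y(t) = fixed part + u(j) + v(ij) + e(ijt). The gain is y(1) − y(0) = fixed part + e(ij1) − e(ij0); u and v are gone. With complete balanced data, the arm × time test is then a two-sample t-test on student gains that ignores classroom. This was checked by fitting mixed models to three simulated datasets with a gain ICC of 0.20:

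| Dataset | SE, intercepts only | SE, t-test on gains | SE, with classroom × time |
|---|---|---|---|
| 1 | 0.0895 | 0.0895 | 0.0998 |
| 2 | 0.0849 | 0.0849 | 0.1035 |
| 3 | 0.0945 | 0.0945 | 0.1245 |

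**Step 3: type I error.** The true variance of the arm difference in mean gain is about 1 + (m − 1)ρ times the variance the model assumes. Hence type I error = 2 × [1 − Φ(1.96/√(1 + 3ρ))] for m = 4. For example, at ρ = 0.20, 1.96/√1.6 = 1.55, which gives 12.1%. Simulation used 20,000 null trials per setting with 35 v 34 classrooms of 4:

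| ρ | 1 + 3ρ | Formula | Simulated, intercepts only | Simulated, classroom-level test |
|---|---|---|---|---|
| 0 | 1.00 | 5.0% | 4.8% | 4.7% |
| 0.02 | 1.06 | 5.7% | 6.0% | 5.3% |
| 0.05 | 1.15 | 6.8% | 6.8% | 5.0% |
| 0.10 | 1.30 | 8.6% | 8.5% | 5.0% |
| 0.20 | 1.60 | 12.1% | 12.0% | 5.0% |
| 0.30 | 1.90 | 15.5% | 15.6% | 5.0% |

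With five students per classroom, also within the recruitment goal, the formula gives 7.4%, 9.8% and 14.4% at ρ = 0.05, 0.10 and 0.20.

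**The case against.** The strongest reply is that the article names levels of nesting, not a covariance structure. A random effect for classroom in a longitudinal model can include a classroom time effect, which is exactly the term in question. A condensed article may leave that detail, and the degrees-of-freedom method, to a fuller plan that is not shown. The power section shows that the authors had clustering in mind. All of this stands, and it is why the point is conditional. It does not remove the point: the article does choose to print the random effects of its primary model, and an analyst following that wording in the plainest way would lose the classroom from the test. With two time points a student slope cannot be separated from residual error, so the student effect is in practice an intercept, and the parallel wording for classroom suggests the same.

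A second reply is that arm × time is nowhere named as the primary contrast. That is also true. It is inferred from the outcome being a gain, from analysis over time, and from the three-way moderator term.

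A third reply concerns size. A reader might take the plan's ICC of 0.2 as the ICC of gains and conclude that the test runs at 12%. The article does not support this: it does not identify the 0.2 as an ICC of gains, and stable differences between classrooms drop out of gains, so the two can differ.

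A reader might also infer that the power section describes an end-of-year comparison adjusted for baseline. It says neither; it mentions only one covariate explaining 15% of the variation.

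**Conclusion.** The point holds in conditional form. If the model is fitted with random intercepts for classroom and student only, and arm × time is the treatment effect, the primary test is anticonservative whenever gains cluster by classroom. With four students per classroom, true type I error at a nominal 5% is about 5%, 7%, 9% and 12% for assumed gain ICCs of 0, 0.05, 0.10 and 0.20. At 0.20 the standard error is too small by a factor of √1.6 = 1.26. The figures rest on complete balanced data and on gain ICCs that are assumed.

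A reader might go further and say that the plan definitely omits classroom variation in gains and that its error rate is inflated. The text does not carry that: it does not exclude a classroom time effect, and there is no inflation if the gain ICC is zero. What can be said is that the model as printed does not secure the 5% level that the power section assumes.

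**What to change.** State the primary model in one of two ways:

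- keep the longitudinal model, name arm × time as the primary contrast, and add a classroom-by-time random effect; or
- analyse end-of-year DAS-II by arm, with baseline DAS-II as a covariate and a random intercept for classroom.

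In either case use classroom-based degrees of freedom (69 − 2 = 67 for a simple classroom-level comparison), and use the same model for the Bracken, ABAS-II and PDD-BI. The two options are not identical, so choose one in advance. It would also help to say which outcome scale the ICC of 0.2 refers to, so that the power statement and the model can be matched.

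This changes the analysis wording only and needs no new data. If a classroom time effect is already intended, one sentence settles it. The cost is wider confidence intervals than under the intercept-only model: by factors of about √1.15 = 1.07, √1.30 = 1.14 and √1.60 = 1.26 at gain ICCs of 0.05, 0.10 and 0.20.

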**Methods:**

This study protocol describes a type II hybrid cluster randomized effectiveness-implementation trial. We will train and coach 70 teachers in autism support classrooms in one large school district in the use of evidence-based practices for students with autism. Half of the teachers then will be randomly selected to receive training and access to TeachTown: Basics, a CAI for students with autism, for the students in their classrooms. The study examines: (1) the effectiveness of TeachTown for students with autism; (2) the extent to which teachers implement TeachTown the way it was designed (i.e., fidelity); and (3) whether its uptake increases or reduces the use of other evidence-based practices.

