### Participants

#### Teachers

Teachers in the School District of Philadelphia’s K-2 autism support classrooms (*n* = 83) will be recruited. Teachers will participate in TeachTown training as part of their professional development but will not be required to participate in this study. We anticipate recruiting 80% of teachers (69 classrooms). Teachers will be randomly assigned to one of two conditions during year 1 of the study: TeachTown and waitlist. Teachers in the waitlist condition will receive training and support in the use of TeachTown in year 2 of the study.

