### Data collection

The TeachTown company will provide anonymized monthly data on all students’ use of TeachTown. These data, aggregated to the classroom level, will allow us to measure penetration for all students in the classroom. Independent variables, including intentions and determinants of intention, will be measured immediately following the 2-day TeachTown training, so that teachers will have familiarity with the program before answering these questions.

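### The Aim 1 three-way moderator test cannot be estimated for penetration or TeachTown fidelity, which do not vary or do not exist in the year-1 control arm, and it is not a clean moderator test for EBP use

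*Protocol article*

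**What the plan says.** The Data analyses section under Aim 1 lists six potential moderators of TeachTown impact: baseline symptoms (PDD-BI), baseline cognitive functioning (DAS-II), "penetration (whether the consented student received TeachTown instruction based on the electronic logs"), "fidelity of program implementation (direct observation of generalization lessons, described in aim 2"), "use of the EBPs described in Aims 3", and family characteristics. One model serves all six: "Potential moderators will be included in the model as main effects and as interaction terms with time and treatment group factors in the model". One test serves all six: "The three-way interaction between time, treatment group, and the moderator will be used to assess the presence and magnitude of the moderating effect". No exception is made for any of them.

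On who has TeachTown and when, the abstract's Methods paragraph says "Half of the teachers then will be randomly selected to receive training and access to TeachTown: Basics", and the Teachers section says "Teachers in the waitlist condition will receive training and support in the use of TeachTown in year 2 of the study". Table 1 and the Measures and Data collection sections under Aim 1 place the DAS-II, Bracken, ABAS-II and PDD-BI at the beginning and end of year 1 only.

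On the usage logs, the Data collection section under Aim 2 says "The TeachTown company will provide anonymized monthly data on all" students' use of the program, to be aggregated to the classroom.

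**The concern.** A three-way term asks whether the arm difference in change over time depends on the moderator. The moderator must therefore take different values within each arm. A baseline characteristic does. Receipt of TeachTown and quality of TeachTown delivery do not, because in the Aim 1 data the control arm has none of either.

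An analyst who follows the text will meet a model that cannot be fitted as written and will have to improvise after seeing data. Whatever coefficient survives compares users with non-users, or well-run with poorly run classrooms, within one arm. Reported as moderation of TeachTown impact, it would invite the conclusion that the program works when used well, although better teachers or faster-learning students could produce the same pattern with no program effect.

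EBP use raises a lesser problem. It exists in both arms, but it is observed during the year, and Aim 3 is built on the possibility that TeachTown alters it.

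**Working it through.** The plan gives no figure for this point, so the check is whether the stated model is identified.

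**Inputs from the protocol.** 35 TeachTown and 34 control classrooms (Aim 1, Data analyses); 276 students, which is 4 per classroom (Children and their families); two outcome times, both in year 1 (Table 1); no TeachTown in control classrooms until year 2 (Teachers).

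**Stated fixed effects.** Let G = arm (1 = TeachTown), T = time (0, 1) and M = moderator. The eight columns are 1, T, G, M, T×G, T×M, G×M and T×G×M.

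**Penetration or fidelity, controls coded 0.** M = 0 whenever G = 0. Then G×M = M and T×G×M = T×M. Two columns duplicate two others, so the rank is 8 − 2 = 6. Whichever duplicate the software keeps, and whatever label it prints, the coefficient is the M-related difference in change within the TeachTown arm.

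**Fidelity, controls missing.** All control rows drop out, leaving 35 × 4 × 2 = 280 records with G = 1 throughout. G equals the intercept, T×G = T, G×M = M and T×G×M = T×M, so the rank is 4.

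**Numerical check.** Building the matrix for 276 students at two times gave:

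| Moderator | Rank of 8 |
|---|---|
| Baseline variable | 8 |
| EBP use | 8 |
| Penetration, controls 0 | 6 |
| TeachTown fidelity, controls 0 | 6 |
| TeachTown fidelity, controls missing | 4 |

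If a few control students did log in (3 assumed), the rank returns to 8, but the term then rests on those few students.

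**Size of possible confounding, fidelity.** Assume no TeachTown effect, gains with SD 1, a classroom share of gain variance of 0.2, and correlation ρ between teacher quality and fidelity. The protocol's ICC of 0.2 is for student outcomes; using it for gains is an assumption, and the protocol gives no ρ. Splitting TeachTown classrooms at the median of fidelity, with a half-normal mean of 0.80:

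spurious high-minus-low gap = 2 × √0.2 × 0.80 × ρ ≈ 0.71ρ

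- ρ = 0.1: about 0.07 SD
- ρ = 0.3: about 0.21 SD
- ρ = 0.5: about 0.36 SD

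**Size of possible confounding, penetration.** A separate simulation with no TeachTown effect assumed that about 69% of TeachTown students use the program, and that the tendency to use it correlates 0.7 with a latent growth factor worth b SD of gain. The apparent effect of use was 0.48 SD at b = 0.4 and scales at about 1.17 × b, so about 0.12 SD at b = 0.1. These are also illustrations on assumed inputs.

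**EBP use.** The term is estimable. The direction and size of any bias depend on inputs the protocol does not give. One assumed scenario with no TeachTown effect gave a mean interaction of −0.03 and 5.7% rejection at the 5% level, so a large bias is not demonstrated.

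**The case against.** **These are secondary analyses.** The power section calls moderation a secondary goal, and the comparison of 35 with 34 classrooms does not use these terms. This stands and limits the weight of the point. A reader might infer that the effectiveness analysis or the whole moderator plan is compromised. It is not: baseline symptoms, baseline cognition and family characteristics are unaffected.

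**The analysis plan may sort it out.** An article can leave coding and missing-data rules to a fuller document. Here, however, the model and the test are stated and applied to all six moderators. The growth mixture step in the same section does not help, because controls have no TeachTown fidelity trajectory to classify. The Aim 3 device of pooling each classroom's first TeachTown year is not open to Aim 1, since student outcomes stop after year 1.

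**EBP use is not shown to be a mediator.** This stands. A reader might infer from Aim 3 that it is one. Aim 3 predicts less one-to-one teaching and data collection, no change in reinforcement, behavior correction or visual schedules, and also tests a competing hypothesis of increased use. A mediator must in addition affect the student outcome. The documents support only that EBP use is a post-randomization variable that treatment may change.

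**The logs may be linkable.** A reader might infer from the word anonymized that penetration can never be joined to a student's DAS-II. The Aim 2 text concerns all students, aggregated to classroom level, and does not exclude a coded extract for those who consented. The two passages need reconciling, no more.

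**Conclusion.** The point holds for penetration and TeachTown fidelity. As written, their three-way terms are not separately estimable. This follows from the design alone, given no TeachTown use in year-1 control classrooms, and needs no distributional assumption. What can be estimated is a non-randomized contrast within the TeachTown arm. Its bias is unknown; the range of 0.07 to 0.36 SD for fidelity depends on the assumed correlation of 0.1 to 0.5 and on a classroom share of gain variance of 0.2, and should not be read as a prediction.

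For EBP use the verdict is milder: the term can be fitted, but it is not a clean test of effect modification.

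The stated 80% power for moderators at d = 0.65 cannot apply to penetration or fidelity, because a term that is not identified has no power to calculate.

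**What to change.** 1. Restrict the time × group × moderator test to baseline variables: PDD-BI, DAS-II and family characteristics.
2. Analyse penetration and TeachTown fidelity within the TeachTown arm only, labelled exploratory and observational.
3. Optionally, add a complier-average estimate for penetration as a sensitivity analysis, with its exclusion restriction stated. That restriction requires assignment to act on outcomes only through the student's receipt of TeachTown, which a change in EBP use in the same classroom could breach. The method does not carry over to fidelity, which is a graded trajectory and not yes/no receipt.
4. Report EBP use during the year as an exploratory or mediation analysis.
5. State that the d = 0.65 power statement does not cover penetration or TeachTown fidelity.
6. State how the logs of consented students are linked to their study records, given the anonymized extract described under Aim 2.

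Items 1 to 5 are changes of wording. Item 6 needs a sentence and, if no link exists yet, a coded identifier in the vendor extract for consented students. The price is that penetration and fidelity results carry a weaker, non-causal label.
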